## Abstract

**Background:**

Fortification of human milk is a standard practice for feeding very low birth weight infants. However, preterm infants often still experience suboptimal growth and feeding intolerance. New fortification strategies and different commercially available fortifiers have been developed. Commercially available fortifiers are constituted by a blend of ingredients from different sources, including plant oils and bovine milk proteins, thus presenting remarkable differences in the quality of macronutrients with respect to human milk. Based on the consideration that donkey milk has been suggested as a valid alternative for children allergic to cow’s milk proteins, due to its biochemical similarity to human milk, we hypothesized that donkey milk could be a suitable ingredient for developing an innovative human milk fortifier.

The aim of the study is to evaluate feeding tolerance, growth and clinical short and long-term outcomes in a population of preterm infants fed with a novel multi-component fortifier and a protein concentrate derived from donkey milk, in comparison to an analogous population fed with traditional fortifier and protein supplement containing bovine milk proteins.

**Methods:**

The study has been designed as a randomized, controlled, single-blind clinical trial. Infants born <1500 g and <32 weeks of gestational age were randomized to receive for 21 days either a combination of control bovine milk-based multicomponent fortifier and protein supplement, or a combination of a novel multicomponent fortifier and protein supplement derived from donkey milk. The fortification protocol followed is the same for the two groups, and the two diets were designed to be isoproteic and isocaloric. Weight, length and head circumference are measured; feeding tolerance is assessed by a standardized protocol. The occurrence of sepsis, necrotizing enterocolitis and adverse effects are monitored.

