Human milk is the recommended form of enteral nutrition for all neonates including preterm infants [5]. Breast milk alone, however, does not meet the recommended nutritional needs for growth in preterm infants [6, 7]. The most common strategy in neonatal care facilities is to cope with these potential nutrient deficits by supplementing breast milk with additional nutrients (mainly proteins and minerals) to ensure a sufficient caloric intake in consideration of the special nutritional requirements [8–10]. The fortification of human milk still represents a significant challenge [11, 12]. The standard fortification strategies have been considered unsatisfactory to sustain an appropriate growth. Thus, new approaches were developed, among which Adjustable (ADJ) Fortification currently seems to be the most promising [13]. It involves the use of a protein supplement on an individualized basis, in addition to a multi-component fortifier. This method, accepted at an international level, consists of providing a variable protein intake based on the metabolic response of each single newborn by titration to the infant’s blood urea nitrogen level [14, 15]. This approach requires simple, high-quality and well-tolerated protein supplements which, unfortunately, are not readily available. Most commercially available multi-nutrient fortifiers are derived from bovine milk, which has a protein composition very different from that of human milk. Moreover, cow milk protein intake in the first months of life has raised concerns because of its association with allergies [16] and some studies have observed a possible role of cow’s milk proteins as a trigger of intestinal inflammation in preterm neonates. [17] Investigations on exclusive HM diets (human milk-based fortifier and donor HM, if mother’s milk unavailable) have been carried out in recent years. All these studies recently underwent to a systematic review [18]; most of them were retrospective studies and not randomized clinical trials. Authors conclude that there is not strong evidence that human milk based fortifiers in otherwise exclusively human milk-fed preterm infants affect important outcomes. Consistently, milk from mono-gastric animals, rather than from ruminants, has been suggested during recent years to be more suitable for human nutrition based on their physiochemical properties [19]. In previous studies, our group observed on children affected by cow milk protein allergy that donkey milk (DM) was highly tolerated [20], and found that its protein and lipid fractions showed a substantial similarity to that of human milk [21, 22]. DM has an n-3 PUFA (polyunsaturated fatty acids) content equivalent to human milk, and is rich in lysozyme, a protein characterized by antibacterial properties, able to hinder pathogen growth, and milk spoilage. It has been recently demonstrated in murine models that a supplementation of the basal diet with DM decreases the accumulation of body lipids and affects glucose and lipid metabolism in a manner more similar to human milk than cow milk [23] These biological effects resulted comparable with those elicited by human milk [24] Based on the above considerations, it can be speculated that DM is more suitable than bovine milk to be an ingredient of a human milk fortifier for VLBW Infants and preterm newborns.

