
Our hypothesis is that feeding these newborns according to ADJ fortification principles, with human milk fortified by protein and multi-component supplements derived from DM, will improve the feeding tolerance and the clinical, metabolic, neurological and auxological outcome at short- and long-term.

We present the protocol of a study aimed to evaluate the use of DM-derived multi-component fortifier and protein concentrate for the nutrition of infants with birthweight <1500 g or gestational age < 32 weeks. This evaluation is being performed through a clinical trial (randomized, controlled, blind) by comparing it with commercial bovine milk-based multi-component fortifier and protein concentrate.

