### Study design

Infants meeting inclusion criteria are identified and their parents approached for consent. After informed written parental consent is obtained, infants are randomized 1:1 by a software-generated list in one of the following groups:Control group: Adjustable Fortification with commercial multi-component fortifier (FM85 Nestlè) and protein concentrate (Protifar Nutricia), named BMC and BPC respectively, derived from bovine milk, for a minimum of 21 days (if necessary, fortification is continued after this period using the same type of product)Fortilat group: Adjustable Fortification with multi-component fortifier and protein concentrate derived from donkey milk, named DMC and DPC respectively, not commercially available, and prepared according to current EU legislation on Foods for special medical purposes, for a minimum of 21 days (if necessary, fortification is continued after this period using the same type of product).

The composition of BMC and DMC are provided in Table 1. Table 2 presents the composition of BPC and DPC. The experimental products were produced by ultrafiltration of pasteurized donkey milk in a pilot stainless steel plant. Retentates from the ultrafiltration processes were then pasteurized and aseptically lyophilized and packed. All the batches used for the trial were analyzed for the microbiological and chemical profile and complied with the safety criteria required by Italian legislation. The products are stored at −80 °C until used.

**Table 1 Tab1:** Macro-composition of the multi-component fortifiers derived from bovine milk (BMC) and from donkey milk (DMC). Values per 100 g of product

	BMC	DMC
Protein g (Nx6.25)	20.0	22.5
Carbohydrate g	66.0	59.0
of which:		
Lactose g	6.0	59.0
Maltodextrine g	60.0	0.0
Fat g	0.4	3.6
Energy:		
Kcal	385	390
kcal/g protein	18.8	15.6
Calcium mg	1500	938
Phosphate mg	900	734
Osmolality mOsm/Kg	453	441

**Table 2 Tab2:** Composition of the protein concentrates derived from bovine milk (BPC) and from donkey milk (DPC). Values per 100 g of product

	BPC	DPC
Protein g (Nx6.25)	88.5	43
Carbohydrate g	<1.5	33.5
Fat g	≤2.0	6.1
Energy Kcal	370	418
Calcium mg	1350	1650
Phosphate mg	700	1150

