A nutrition protocol following the criteria of ADJ fortification is being followed to ensure that fortification advancement is consistent for all study participants. Tables 3 and 4 show the ADJ Fortification criteria for the control products (BMC and BPC) and for the test products (DMC and DPC). Since the protein concentration and energy content of the bovine milk based products differ from the donkey milk based products, the amounts of powder required to obtain the same level of fortification are different depending on the product in use (Table 4). Because the same nurses in charge of feeds preparation and administration are also in charge of evaluating signs of feeding tolerance, it is not possible to achieve a double blindness of the intervention. As caregivers are aware of the group allocation of infants, this is to be defined as a single-blind randomized controlled trial.

**Table 3 Tab3:** Adjustable Fortification criteria based on weekly blood urea nitrogen (BUN) values

BUN (blood urea nitrogen)	
< 10 mg/dl	Increase fortification by one level
10–16 mg/dl	No change
> 16 mg/dl	Decrease fortification by one level

**Table 4 Tab4:** Amount of fortifer and protein supplement at the various fortification levels, according to ADJ fortification protocol

	Multicomponent			Protein concentrate	
Levels	BMC g/ml	DMC g/ml		BPC g/ml	DPC g/ml
2.5%	0.025	0.02		–	–
4%	0.04	0.032		–	–
5%	0.05	0.04		–	–
5% +1	0.05	0.04	+	0.004	0.008
5% +2	0.05	0.04	+	0.008	0.016
5% +3	0.05	0.04	+	0.012	0.024

Advancing of enteral feeds is strictly regulated according to the feeding protocol adopted in our NICU, based on the evaluation of signs of feeding intolerance (available on demand to the authors). The criteria for hospital discharge are uniform, i.e., satisfactory weight gain while receiving full oral feeding, maintenance of adequate thermal stability and resolution of acute medical conditions.

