### Outcome measures

Primary Endpoint.Occurrence of at least one episode of feeding intolerance, defined as interruption of enteral feeding for at least eight consecutive hours during the observation period.Secondary Endpoints.2.1 Gastrointestinal outcomes: Number of feeding intolerance episodes, number of feeding interruption episodes (of any duration), total hours of enteral feeding interruption, time required to reach full enteral feeding (150 ml/kg/day).2.2 Gastric Emptying time (ultrasonic measurements of the antral cross sectional area) [25, 26]: half-time of gastric emptying (minutes) and time of gastric emptying (minutes).2.3 Esophageal impedance and pH monitoring (MII/pH) [27, 28]: GER frequency (reflux events/h), bolus reflux extent (number of channels), Bolus clearance time (seconds), bolus exposure index and reflux index (percentage).2.4 Clinical outcomes: necrotizing enterocolitis, suspected or confirmed sepsis, mortality, hospital stay duration, intraventricular hemorrhage, retinopathy of prematurity (defined according to the Vermont Oxford Network) [29].2.5 Metabolic and auxological outcomes (as shown in the synoptic table) (Table 5).

**Table 5 Tab5:** Synoptic table. T0: before starting the fortification; T1: day 7 after beginning the fortification (if level 3 of ADJ fortification) or as soon as level 3 is reached; T2: day 14 since beginning of fortification; T3: day 21 since beginning of fortification

	STUDY PERIOD						
	Enrolment	Allocation	Post-allocation				Close-out
Timepoint			T0	T1	T2	T3	
Enrolment:							
Eligibility screen	X						
Informed consent	X						
Full patient history collection	X						
Allocation		X					
Intervention:							
BUN			X	X	X	X	
Albumin			X	X	X	X	
Creatinine			X	X	X	X	
Calcium			X	X	X	X	
Phosphate			X	X	X	X	
Alkaline Phosphatase			X	X	X	X	
Weight			X	X	X	X	
Lenght			X	X	X	X	
Head circumference			X	X	X	X	
Plasma Aminoacids			X			X	
Urine Aminoacids			X			X	
Urinary Metabolomic Profile			X			X	
Calprotectin			X			X	
pH			X	X	X	X	
BE			X	X	X	X	
HCO_3_^−^			X	X	X	X	
MII/pH						X	
Gastric emptying time						X	
Assesments							
List other data variables							X
List other data variables							X

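### The dosing table does not make the diets isocaloric: as printed, the donkey-milk arm gets 19% less fortifier energy at the first three levels, and Table 1's energy-to-protein row contradicts its own entries

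*Protocol article*

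**What the plan says.** The abstract (Methods) says that "the two diets were designed to be isoproteic and isocaloric". In Study design, the text before Tables 3 and 4 notes that the two product lines differ in protein and energy content, so that "the amounts of powder required to obtain the same level of fortification are different depending on the product in use". Table 4 is thus the stated means of equalising the arms.

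Table 1 gives protein and energy per 100 g of the multi-component fortifiers, with a row headed "kcal/g protein". Table 2 does the same for the protein concentrates (BPC bovine, DPC donkey), without the ratio row. Fortification is adjustable, "providing a variable protein intake based on the metabolic response of each single newborn", with levels moved weekly on blood urea nitrogen (Table 3).

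The Background hypothesis is that the donkey-milk products "will improve the feeding tolerance and the clinical, metabolic, neurological and auxological outcome", and the secondary endpoints include "Metabolic and auxological outcomes (as shown in the synoptic table").

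**The concern.** Two powders with nearly the same energy per gram cannot deliver the same energy when one is dosed at four-fifths of the other. Unless the concentrates make up the difference, the arms differ in energy by design. At the first three levels there is no concentrate to do so.

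This matters for growth and metabolic outcomes. A reader who accepts the equal-energy statement will attribute any difference in weight, length or head circumference to the source of the milk. If energy supply also differs by arm, that attribution is not available. The inconsistent ratio row adds a second problem: at least one cell in each column of Table 1 is wrong, so the reader cannot tell whether equal protein was achieved either.

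**Working it through.** **Inputs.** Table 1, per 100 g: BMC 385 kcal, 20.0 g protein; DMC 390 kcal, 22.5 g protein; printed ratios 18.8 and 15.6 kcal per g protein. Table 2, per 100 g: BPC 370 kcal, 88.5 g protein; DPC 418 kcal, 43 g protein. Doses are from Table 4. The full feeding volume of 150 ml/kg/day is from Outcome measures. Milk energy is not given, so 60–70 kcal/100 ml is assumed.

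**Step 1: the printed ratio row.** 385/20.0 = 19.25 (printed 18.8); 390/22.5 = 17.3 (printed 15.6). Neither reproduces. Using 4/4/9 kcal/g factors gives 17.4 and 15.9; non-protein energy gives 15.3 and 13.3; a 6.38 nitrogen factor gives 18.9 and 17.0. None yields both printed values. Taken at face value, the ratios imply either protein of 385/18.8 = 20.5 g and 390/15.6 = 25.0 g, or energy of 18.8 × 20.0 = 376 and 15.6 × 22.5 = 351 kcal.

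**Step 2: fortifier energy by level.** With doses in g per 100 ml:

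bovine = BMC × 3.85 + BPC × 3.70; donkey = DMC × 3.90 + DPC × 4.18.

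Whole-diet difference = (M + donkey)/(M + bovine) − 1, with M = 70 and then 60 kcal/100 ml. The last column is the difference × 1.5.

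| Level | Bovine, kcal/100 ml | Donkey, kcal/100 ml | Fortifier energy | Whole diet | kcal/kg/day at 150 ml/kg/day |
|---|---|---|---|---|---|
| 2.5% | 9.63 | 7.80 | −19.0% | −2.3 to −2.6% | −2.7 |
| 4% | 15.40 | 12.48 | −19.0% | −3.4 to −3.9% | −4.4 |
| 5% | 19.25 | 15.60 | −19.0% | −4.1 to −4.6% | −5.5 |
| 5%+1 | 20.73 | 18.94 | −8.6% | −2.0 to −2.2% | −2.7 |
| 5%+2 | 22.21 | 22.29 | +0.4% | +0.1% | +0.1 |
| 5%+3 | 23.69 | 25.63 | +8.2% | +2.1 to +2.3% | +2.9 |

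Example, 5% level: (60 + 15.60)/(60 + 19.25) − 1 = −4.6%.

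**Step 3: could a misprinted energy cell explain it?** At a dose ratio of 0.8, equal energy needs DMC at 385/0.8 = 481 kcal/100 g. If BMC were really 376 or 347.6 (the ratio-row and 4/4/9 values), DMC would need 470 or 434.5. The highest reading of DMC is 390. Every combination of plausible readings was run: BMC 385, 376 or 347.6; DMC 390, 351, 358.4 or 368.4; BPC 370, 378 or 354; DPC 418 or 360.9 (72 in all).

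- First three levels: from 0.8 × 390/347.6 − 1 = −10.2% to 0.8 × 351/385 − 1 = −27.1% of fortifier energy; whole diet −1.1% to −6.6%. The gap never closes.
- Higher levels: about −18% to +1% at 5%+1, −11% to +10% at 5%+2, and −5% to +18% at 5%+3. The sign there is uncertain.

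**Step 4: protein.** With 22.5 g in DMC, added protein at the 5% level is 4 × 0.225 = 0.90 g/100 ml against 5 × 0.200 = 1.00. By level the difference is −10%, −10%, −10%, −8.1%, −7.0% and −6.3%. With 25.0 g it is 0%, 0%, 0%, −0.7%, −1.2% and −1.5%. The 25.0 g reading fits the 0.8 dose ratio exactly, which suggests that dosing was matched on protein and 22.5 is a misprint. In that case energy cannot also match at the first three levels: on the printed ratio row, equal protein means 15.6/18.8 − 1 = −17.0% fortifier energy.

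**The case against.** The abstract speaks of diets, not fortifiers. Most of the energy comes from human milk, so the relevant gap as printed is at most about 5%, shrinks to nothing at 5%+2 and then reverses. The article sets no tolerance for calling diets isocaloric, and uses the word once, in the abstract. The body text claims only the same fortification level, and the tables disclose every input. Levels follow each infant's urea, so the net gap per infant is unknown.

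Much of this is fair, and it limits the weight of the point. The whole-diet figure is the one to judge by, and it rests on an assumed milk energy; at 55–75 kcal/100 ml the 5% level gap would be −4.9% to −3.9%. It does not remove the contradiction. At the first three levels the deficit always runs against the same arm, and it is not obviously confined to a short start-up: Table 5 times its T1 visit to level 3, which on the order of Table 4 is apparently the 5% level, where the gap is largest.

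Two further cautions stand. Which Table 1 cell is wrong cannot be settled from the article, and the ratio row fails for BMC too, so 25.0 g is an inference. Whole-diet protein differences are also smaller than the added-protein figures: with milk protein assumed at 1.0–1.5 g/100 ml and 22.5 g in DMC, they are −2.5% to −5.0%.

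**Conclusion.** The concern holds. The equal-energy property does not follow from the composition and dosing tables. The 19% fortifier deficit at the first three levels needs no assumption beyond the printed cells, and no plausible reading of the energy cells brings it below about 10%. The whole-diet figures (about 4–5% less at 5%, about 2% more at 5%+3) assume milk at 60–70 kcal/100 ml. The sign at the higher levels is not certain. Table 1's ratio row is wrong against its own entries in both columns, and whether the diets are isoproteic depends on which cell is corrected.

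The effect is modest. It limits what can be concluded from the growth and metabolic secondary endpoints. The primary endpoint, the Fisher test and the sample size are unaffected. This should be fixed.

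**What to change.** - Correct Table 1. Check the DMC entries against the batch records (the article says "All the batches used for the trial were analyzed for the microbiological and chemical profile") and the BMC entries against the manufacturer's composition, then recompute the ratio row.
- Replace the isocaloric claim with a statement of the energy difference at each fortification level. Keep the isoproteic claim only if 25.0 g protein per 100 g DMC is confirmed.
- Interpret growth and metabolic secondary endpoints as effects of the products as dosed, and report delivered protein and energy intake by arm where feeding records allow.

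The cost is a check of a few table cells and a change of wording. The claim of equality becomes weaker; dosing, design and the primary analysis stay as they are.

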**Discussion:**

This is the first clinical study investigating the use of a human milk fortifier derived from donkey milk for the nutrition of preterm infants. If donkey milk derived products will be shown to improve the feeding tolerance or either of the clinical, metabolic, neurological or auxological outcomes of preterm infants, it would be an absolute innovation in the field of feeding practices for preterm infants.

**Trial registration:**

ISRCTN -ISRCTN70022881.

## Background

Very preterm newborns (gestational age < 32 weeks) and Very Low Birthweight Infants (VLBWI, birthweight <1500 g) currently represent the majority of patients assisted in Neonatal Intensive Care Units (NICU) [1]. The increase of the survival rate for these newborns, due to improvements in perinatal care, has opened new perspectives regarding their outcome and has a significant impact on their health status in adulthood.

Although very preterm or VLBWI usually attain some “catch-up” growth following hospital discharge, growth deficits can persist throughout childhood and adolescence, and into adulthood. Slow postnatal growth is associated with neurodevelopmental impairment in later childhood, with poorer cognitive outcomes, and may have consequences for long-term metabolic and cardiovascular health [2–4]. Nutrition represents a fundamental factor for long-term survival and quality of life for this group of infants. The main issue is to ensure an adequate qualitative and quantitative nutrition, particularly in terms of protein intake, which is the main cause of post-natal growth deficit.

Human milk is the recommended form of enteral nutrition for all neonates including preterm infants [5]. Breast milk alone, however, does not meet the recommended nutritional needs for growth in preterm infants [6, 7]. The most common strategy in neonatal care facilities is to cope with these potential nutrient deficits by supplementing breast milk with additional nutrients (mainly proteins and minerals) to ensure a sufficient caloric intake in consideration of the special nutritional requirements [8–10]. The fortification of human milk still represents a significant challenge [11, 12]. The standard fortification strategies have been considered unsatisfactory to sustain an appropriate growth. Thus, new approaches were developed, among which Adjustable (ADJ) Fortification currently seems to be the most promising [13]. It involves the use of a protein supplement on an individualized basis, in addition to a multi-component fortifier. This method, accepted at an international level, consists of providing a variable protein intake based on the metabolic response of each single newborn by titration to the infant’s blood urea nitrogen level [14, 15]. This approach requires simple, high-quality and well-tolerated protein supplements which, unfortunately, are not readily available. Most commercially available multi-nutrient fortifiers are derived from bovine milk, which has a protein composition very different from that of human milk. Moreover, cow milk protein intake in the first months of life has raised concerns because of its association with allergies [16] and some studies have observed a possible role of cow’s milk proteins as a trigger of intestinal inflammation in preterm neonates. [17] Investigations on exclusive HM diets (human milk-based fortifier and donor HM, if mother’s milk unavailable) have been carried out in recent years. All these studies recently underwent to a systematic review [18]; most of them were retrospective studies and not randomized clinical trials. Authors conclude that there is not strong evidence that human milk based fortifiers in otherwise exclusively human milk-fed preterm infants affect important outcomes. Consistently, milk from mono-gastric animals, rather than from ruminants, has been suggested during recent years to be more suitable for human nutrition based on their physiochemical properties [19]. In previous studies, our group observed on children affected by cow milk protein allergy that donkey milk (DM) was highly tolerated [20], and found that its protein and lipid fractions showed a substantial similarity to that of human milk [21, 22]. DM has an n-3 PUFA (polyunsaturated fatty acids) content equivalent to human milk, and is rich in lysozyme, a protein characterized by antibacterial properties, able to hinder pathogen growth, and milk spoilage. It has been recently demonstrated in murine models that a supplementation of the basal diet with DM decreases the accumulation of body lipids and affects glucose and lipid metabolism in a manner more similar to human milk than cow milk [23] These biological effects resulted comparable with those elicited by human milk [24] Based on the above considerations, it can be speculated that DM is more suitable than bovine milk to be an ingredient of a human milk fortifier for VLBW Infants and preterm newborns.

Our hypothesis is that feeding these newborns according to ADJ fortification principles, with human milk fortified by protein and multi-component supplements derived from DM, will improve the feeding tolerance and the clinical, metabolic, neurological and auxological outcome at short- and long-term.

We present the protocol of a study aimed to evaluate the use of DM-derived multi-component fortifier and protein concentrate for the nutrition of infants with birthweight <1500 g or gestational age < 32 weeks. This evaluation is being performed through a clinical trial (randomized, controlled, blind) by comparing it with commercial bovine milk-based multi-component fortifier and protein concentrate.

